## 6.0 METHODOLOGY

6.1 Design of Study: We will conduct a three-arm individual-level clinical pilot trial across four clinics. Clinics will be randomized either to adapted Friendship Bench (N = 35 ALWH), enhanced friendship bench (N = 35 ALWH), or standard of care (N = 35 ALWH). Participants will all be recruited and followed for 12 months.

The Adapted Friendship Bench (AFB) will be adapted from the existing Friendship Bench intervention protocol to be youth-friendly and address the unique needs of ALWH. Youth friendly adaptation will include selection of young counselors (mixed genders, aged 20-35) who are motivated to work with young people. Counselors will be trained to deliver non-judgmental counseling that respects the privacy and autonomy of ALWH and enables them to make free and informed choices that are relevant to their individual needs. Training will also include discussion of adolescent development and the unique experiences of ALWH related to stigma, disclosure, social relationship issues, and health care access. Counseling sessions will take place in a youth oriented but discrete location within the HIV clinic and be available on weekends to ensure accessibility. AFB will include 6 individual counseling sessions facilitated by counselors attached to one of the study HIV clinics. The first session includes three components called Opening the Mind, Uplifting, and Strengthening, with subsequent sessions building on the first. Opening the Mind refers to the therapeutic process by which, through asking questions, clients are encouraged to open their minds to identify their problems, choose one to work on, identify a feasible solution, and agree on an action plan through an iterative process guided by the counselor. Each structured session lasts 30-45 minutes and will be conducted in a private clinic room in the participant's local language (Chichewa). No specific retention support will be provided, but participants may identify barriers to engagement in HIV care to address during their counseling session. After 4 sessions of individual therapy, the counselor can refer participants not improving or with suicidal ideation to a supervisor trained in mental health to reassess and manage the case. Case management may include additional counseling or pharmacotherapy, at the discretion of the managing clinician.

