The Enhanced Friendship Bench (EFB) will include all elements of AFB but will additionally integrate peer support via in person group meetings to facilitate engagement in care for ALWH and depression. Peer supporters will be mature young adults (aged 18-21) who have completed secondary school, are openly living with HIV, and motivated to work with adolescents. The counselors must be willing to maintain participant and colleague confidentiality and sign a confidentiality agreement. Peer Supporters will be trained to deliver youth-friendly group sessions related to HIV care. The content of the 6 peer support sessions includes: Mental Health and HIV, Status Communication, Adherence and Viral Load Testing, Secondary Prevention (Sex and Relationships), Stigma, and Planning for the Future. The 6 sessions will be delivered monthly over 6 months and last 90 minutes each. The group sessions will be in a private space in the clinic in the participant's local language (Chichewa).

Standard of Care (SOC) for mental health in public facilities in Malawi includes options for basic supportive counseling by the primary provider or nurse, medication management by the primary provider, referral to the clinic psychiatric nurse or mental health clinic (most clinics have either an assigned psychiatric nurse or a mental health clinic that visits on a rotating basis), or in more severe cases referral to the psychiatric units at tertiary care hospitals (in the Lilongwe region, this is Bwaila Hospital). For this study, standard care will be enhanced by a trained study nurse who will provide mental health evaluation; brief supportive counseling; information, education, and support on depression; and (if indicated) facilitation of referral to the clinic's psychiatric nurse or mental health clinic or to Bwaila Hospital. The study nurse will have up to 3 follow-up contacts with the participant to assess whether they have followed up on recommended referrals or treatment plans and to assess whether any further outreach is indicated.

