## 7.0 ETHICAL CONSIDERATIONS

### 7.1 Human Subjects

Safety considerations. Study staff will evaluate patients for safety who endorse any level of suicidal ideation whether or not they enroll in the study. Safety assessment results will be conveyed to the clinical team as appropriate for further follow-up according to the clinic's standard operating procedures.

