Addressing Harms. Our overall goal is to protect the well-being of ALWH, thus if sexual or physical abuse is reported, we will ensure ALWH are referred to a local organization that deals with sexual abuse/violence so that the individual receives appropriate care or to a local social worker. If a study team member comes to believe that a participant is experiencing a crisis (which the participant may or may not recognize) they also may refer to local social workers for counseling or psychosocial support. Examples would include a participant who is having an extreme emotional reaction when discussing the challenges of living with HIV, or a participant whose behavior suggests possible undiagnosed mental illness. These revelations of harm are not common but may occur on a limited basis, necessitating that study protocols be in place to respond appropriately.

At each clinic from which we will recruit participants, we will identify a provider to act as the “clinic lead” for navigation services. This person is a chief point of contact for the study team. When a situation arises where study staff learns of a potential risk of harm to a participant, the following steps will be followed:

- (1) The study team member learning of the problem will immediately inform the PI.
- (2) If the participant is actively in distress and at the clinic, the study team member will refer the participant to the clinic lead (or, if the lead is not available, to another clinic provider) for immediate evaluation.
- (3) If the participant is actively in distress and not at the health center, the study team member will offer to meet the participant and accompanying them to the health facility for immediate referral.

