- (4) If the participant is not actively in distress, then the study investigators, project manager, and other appropriate project supervisory staff will develop a plan for referring the participant to the clinic lead. As appropriate, the project team may consult the clinic lead in developing the plan. (All consent forms will note that investigators may need to break confidentiality when there is a threat of harm to self or others.) The timing and most appropriate means of effecting a referral will be dependent on the nature of the problem. For example, if a participant reports child abuse in the home, then it would be necessary to involve appropriate social services to investigate the problem. By contrast, if a participant reports that she/he is facing ongoing (but not life threatening) emotional abuse from a partner, then it may make more sense for the navigator to first approach the participant and encourage her/him to meet with a clinic provider or with other social support services in the area.
- (5) Study investigators will inform all governing IRBs of the incident and update the IRBs as necessary on the outcomes of efforts to intercede and resolve the harm.

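### Section 6.1 times the counselor's referral of suicidal ideation to the mental-health supervisor after session 4, as for non-improvement, and does not reconcile this with sections 7.1 and 7.3

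*Protocol*

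**What the plan says.** Protocol section 6.1 describes the Adapted Friendship Bench (AFB) as six individual sessions with a counselor and then gives the route to more specialised care: "After 4 sessions of individual therapy, the counselor can refer participants not improving or with suicidal ideation to a supervisor trained in mental health". The sentence goes on to say that the supervisor reassesses the case and takes over its management, which can extend to more counseling or drug treatment as the managing clinician decides. The Enhanced Friendship Bench (EFB) "will include all elements of AFB but will additionally integrate peer support", so the same rule applies there.

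Two later sections also bear on suicidal ideation, in all arms:

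- Section 7.1: "Study staff will evaluate patients for safety who endorse any level of suicidal ideation whether or not they enroll in the study". Results go to the clinical team where appropriate, for follow-up under the clinic's own procedures. No session number and no time limit is given.
- Section 7.3: "When a situation arises where study staff learns of a potential risk of harm to a participant, the following steps will be followed". Step 1 is "The study team member learning of the problem will immediately inform the PI". In step 2, for a participant in active distress at the clinic, the team member "will refer the participant to the clinic lead (or, if the lead is not available, to another clinic provider) for immediate evaluation". Step 4 is for participants without active distress: "If the participant is not actively in distress, then the study investigators, project manager, and other appropriate project supervisory staff will develop a plan". The plan concerns referral to the clinic lead, and "The timing and most appropriate means of effecting a referral will be dependent on the nature of the problem".

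Section 6.1 does not refer to 7.1 or 7.3, and neither of them refers back to it.

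**The concern.** The two triggers in the section 6.1 sentence differ in kind. Non-improvement can only be judged after some treatment has been given, so a review after the fourth of six sessions is reasonable. Suicidal ideation can be disclosed at the first session and needs no observation period. The protocol gives no reason for putting both under the same condition.

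What is at stake is access to one particular resource. In the AFB and EFB description, the supervisor is the step that brings in someone trained in mental health, with the option of more counseling or medication. A counselor who reads section 6.1 as written could take that step to be available for ideation only from session 4 onwards. The participants are aged 13 to 19 and entered with a BDI-II score of at least 13 (section 6.3). Under section 6.6 the PHQ-9 is taken at every counseling session, so the plan collects information on depressive symptoms before the point at which section 6.1 mentions referral.

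**Working it through.** **Scope of the clause.**

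- Inputs: 35 participants planned in each of AFB, EFB and standard of care (section 6.1); 105 in total (section 6.3); EFB contains all of AFB (section 6.1).
- The plan's own total: 35 + 35 + 35 = 105, which agrees.
- Participants under the clause: 35 (AFB) + 35 (EFB) = 70.
- Share: 70 / 105 = 66.7%.
- Not under the clause: 105 − 70 = 35 (standard of care). That arm has its own route through a study nurse, with no session threshold.

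**The three provisions side by side.**

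| | 6.1 (AFB, EFB) | 7.1 (all arms) | 7.3 (all arms) |
|---|---|---|---|
| Trigger | Non-improvement or suicidal ideation | Ideation at any level | Staff learn of possible harm to a participant |
| Timing | After 4 of 6 sessions | None stated, no session threshold | PI told at once; evaluation at once if in active distress at the clinic; otherwise depends on the problem |
| Force | Permissive (can) | Required (will) | Required (will) |
| Recipient | Mental-health supervisor | Clinical team | PI, then clinic lead |
| Function | Reassess and step up treatment | Safety evaluation | Notification and referral |

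**Reasoning.**

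1. Section 7.1 applies from first contact, because it covers people whether or not they enroll. A safety evaluation therefore does not wait for session 4.
2. Section 7.3 does not name suicidal ideation. Its step 4 does say that consent forms will warn of a possible breach of confidentiality where a person may harm themselves, so self-harm is within its scope.
3. Neither section mentions the supervisor of section 6.1. For that step, the only timing in the protocol is the session-4 condition, and it covers ideation without exception.
4. Section 6.1 says that the counselor can refer after four sessions. It does not say that the counselor cannot refer sooner. The defect is therefore an unsuitable condition attached to one trigger and not reconciled with 7.1 and 7.3. It is not a prohibition.

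The protocol gives no rate of suicidal ideation, so the number of the 70 to whom the condition would matter cannot be derived.

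**The case against.** The strongest reply is that section 6.1 describes stepped care and not the first response to ideation. The supervisor is to reassess, which implies an earlier assessment, and 7.1 and 7.3 supply that assessment in mandatory terms. A permissive later step does not contradict a required earlier one. On this reading only a cross-reference is missing.

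Much of this stands, and it rules out several stronger readings:

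- *That nothing is done about ideation before session 4.* Sections 7.1 and 7.3 show otherwise.
- *That earlier referral is forbidden.* The wording is permissive.
- *That three recipients are a contradiction.* The clinical team, the PI, the clinic lead and the supervisor have different functions, and all may be involved for one participant.
- *That session 4 becomes the default timing for every referral.* It attaches to the supervisor step only. Referral to the clinic lead under 7.3 has its own rule.
- *That the size of the problem is the number of early sessions.* One could compute 70 × 6 = 420 planned individual sessions, of which 70 × 3 = 210 are sessions 1 to 3. These count everyone in two arms and measure neither ideation nor delay. A count of counselors would be no better as a measure of harm.
- *That the arm comparison is biased.* Standard of care has no session threshold, but nothing in the protocol shows a resulting bias.

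Counselor training is planned and clinic procedures are cited, but neither is shown. What counselors will actually be told cannot be judged from this sentence.

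The stepped-care reading does not remove the point. The protocol never says that 6.1 runs in parallel with 7.1 and 7.3. Even if it did, the supervisor step would still carry a session-4 condition for ideation. A cross-reference alone would leave that condition in place.

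**Conclusion.** The point holds as a badly set timing rule in the intervention description. For suicidal ideation, the session-4 condition on referral to the supervisor is unsuitable and is not reconciled with the response that 7.1 and 7.3 already require. It covers the two counseling arms, 70 of 105 planned participants (67%). That figure is the reach of the clause and not a number expected to have ideation or to be harmed, which is unknown.

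The conclusion rests on two readings: that the opening time condition governs both triggers, as the grammar indicates, and that EFB inherits the clause with the rest of AFB, as the protocol says. It does not depend on any assumption about how counselors will behave. The appropriate label is a cheap improvement to a safety instruction.

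**What to change.** In section 6.1:

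1. Limit the after-four-sessions condition to participants who are not improving.
2. Add a sentence to this effect: *suicidal ideation endorsed at any session triggers the response in sections 7.1 and 7.3 at once, and the counselor can refer the participant to the supervisor at that time without waiting for session 4.*

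The supervisor referral should stay permissive, as it is now. Making it compulsory, or setting a same-day limit, would introduce a standard that the protocol does not contain and would need its own justification, including cover for the weekend sessions that section 6.1 foresees.

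The change is to the text of one section. Arms, sample size, visits and analysis stay as they are. The downside is that supervisors may be used earlier in some cases. How often cannot be stated, because the protocol gives no rate of ideation.

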### 2.1 Background and Literature Review

Sub-Saharan Africa (SSA) is home to the largest population of adolescents (10-19 years) living with HIV (ALWH). The 1.46 million ALWH in SSA account for 88% of all ALWH worldwide (1.65 million) and includes individuals who acquired HIV vertically (perinatally) and horizontally (behaviorally). This population is growing due to increasing survival of vertically infected children and increasing rates of horizontal infections among adolescents. In addition, adolescents are the only age group in which AIDS-related deaths are not decreasing in the region. This high burden of morbidity and mortality has led the Joint United Nations Program on HIV and AIDS, the World Health Organization, and NIMH to declare ALWH a priority population requiring immediate attention for research, programming, and policy.

Engaging ALWH in HIV care is critical for maximizing the impact of antiretroviral therapy (ART) on health outcomes, life expectancy, and secondary HIV transmission. The challenge of engaging and retaining ALWH in care is reflected in lower rates of viral suppression and higher rates of loss to follow-up for this group compared to adults and children in SSA. Indeed, such is the case in Malawi, where 3% of the adolescent population is living with HIV (75,000 of 2,257,834 individuals) and estimates of viral suppression among those on ART range from 40%-78%.

Poor engagement in care among ALWH has been attributed to the numerous psychosocial and structural challenges that arise from living with a stigmatized, chronic disease in a low-resource setting during a period of developmental transition - challenges that also increase the vulnerability of ALWH to mental health issues such as depression. Estimates of depression for ALWH in Malawi range from 18%-26%, and depression exacerbates poor engagement in care amongst ALWH. Consequently, addressing depression among ALWH may not only improve mental health but also ART adherence and viral suppression, affording improved individual health outcomes while also acting as secondary prevention among sexually active adolescents.

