**6.2 Place of Study:** The participating health centers will be the Area 18, Area 25, Kawale, and Lighthouse Health Centers. These sites are all government health facilities located in urban Lilongwe, Malawi with ART clinics on their grounds. We selected clinics well matched in terms of staffing levels, services offered, NGO/ancillary program involvement (e.g., all three sites receive training and supervision support from the Lighthouse Trust NGO in Lilongwe), patient volume, and patient population to minimize any important differences between the sites. UNC-Project Malawi will serve as the administrative home for the study and has longstanding relationships with all 4 proposed study sites. UNC Project-Malawi has previously successfully recruited and enrolled adolescents in several sexual and reproductive health studies as well as HIV-related clinical trials.

**6.3 Target Population: ALWH:** We will recruit 105 ALWH from 4 HIV clinics in Lilongwe, Malawi. We aim to recruit for diversity in age, gender identity, and HIV acquisition type. ALWH will be eligible for the study if they are: (1) age 13-19; (2) diagnosed with HIV; (3) scored  $\geq 13$  on the self-reported BDI-II; (4) willing to provide consent (age 18 or 16-17 years old and married (emancipated minors per Malawi law) or assent with parental consent (age 13-17). All HIV+ individuals will be eligible for recruitment including ART initiators, ART re-initiators and established patients. ALWH screening positive for depression who choose not to participate will be referred to a mental health provider.

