#### 6.6 Data Collection Techniques and Tools:

To assess feasibility, sources of data include study visit attendance, counseling session attendance, and peer support engagement logs. To assess acceptability, a brief exit interview and behavioral survey will be conducted. To assess fidelity, a counseling session checklist will be collected. Additionally, to assess preliminary effectiveness, we will measure BDI-II and viral load at enrollment, 6-month visit, and 12-month visit. PHQ-9 will also be measured at enrollment, 6-month visit, 12-month visit, and each counseling session. For viral load testing, trained counselors will collect drops of participant blood from a finger stick prick and put the drops on a blood collection card. The blood spot collection card will be sent to a laboratory to assess viral load and then it will be stored in a freezer at UNC Project Malawi until the end of the study. The collection card will not have the participant's name or other identifying information attached, only their study ID number. Blood collection cards will be destroyed at the end of the study.

Record Availability: The site investigator will make all data abstraction documents and records readily available for inspection by the local IRB as requested.

For the brief exit interview, a semi-structured interview guide will be developed to explore acceptability of the FB and peer support sessions. All interviews will be digitally recorded, transcribed in Chichewa, and then translated into English by study staff according to a transcription protocol. All transcripts will then be reviewed by the interviewer for transcription and translation accuracy.

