##### Secondary Outcomes:

- Effectiveness will be assessed through changes in three outcomes: 1) depression symptoms ( $\geq 50\%$  change in BDI-II scores from enrollment to the end of the study period), 2) retention in care (whether an ALWH attended at least one appointment per quarter), 3) and viral suppression at 12 months (HIV RNA < 1000 copies/mL).

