To assess balance across all 3 study arms at enrollment, we will compare participant characteristics using t-tests for continuous variables and chi-square tests for categorical variables. Quantitative Data: Quantitative measures of feasibility, fidelity, acceptability, and preliminary effectiveness will be summarized using means and standard deviations or proportions and compared across arms using statistical models for continuous or binary outcomes, as appropriate. For feasibility, we will examine the mean number of ALWH enrolled and the proportion of ALWH retained in each of the three study arms (adapted, enhanced, and standard of care). For fidelity, we will examine and compare the proportion of counselors covering at least 80% of checklist items during random direct monitoring sessions across study arms. For acceptability, we will examine and compare the proportion of participants and study staff who found the intervention helpful and easy to deliver across study arms. Changes in depression and engagement in care will be assessed for the 6-month study visit and the 12-month study visit. Generalized estimating equations with an appropriate link for each outcome (i.e., identity link for continuous variables and log link for binary variables) and an exchangeable correlation matrix will be used to examine differences in BDI-II scores, engagement in care, and viral suppression and will account for baseline values of all outcomes and clinic differences. All statistical models will control for any unbalanced confounders. Every effort will be made to minimize missing data, including collecting detailed locator information for the participant as well as for up to two individuals who could help reach the participant should they drop out of contact. However, some missing data is likely to occur. We will examine the data for patterns of missingness and if identified, will conduct sensitivity analyses using inverse probability weights to correct for the bias introduced by the missing data. Qualitative data: Analysis of qualitative exit interview data will involve four steps: 1) reading for content; 2) deductive and inductive coding; 3) data display to identify emerging themes; and 4) interpretation. Codes will be refined during the analysis process and memos will be written for each identified theme.

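### The retention model must adjust for a baseline value that ART initiators cannot have, and ART status enters the HIV-outcome models only if a low-powered balance test flags it

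*Protocol*

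**What the plan says.** Protocol 6.3 sets no limit by treatment stage: "All HIV+ individuals will be eligible for recruitment including ART initiators, ART re-initiators and established patients". No stratification or quota by ART stage is stated.

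Section 6.7 (Secondary Outcomes) lists three effectiveness outcomes. Two concern HIV care: "retention in care (whether an ALWH attended at least one appointment per quarter", and HIV RNA below 1000 copies/mL at 12 months.

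The analysis text in 6.7 gives the adjustment in two parts. The GEE models for BDI-II, engagement in care and viral suppression "will account for baseline values of all outcomes and clinic differences". Then: "All statistical models will control for any unbalanced confounders". Imbalance is assessed at enrollment: "we will compare participant characteristics using t-tests for continuous variables and chi-square tests for categorical variables". ART status is not named there.

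Section 6.6 says "we will measure BDI-II and viral load at enrollment, 6-month visit, and 12-month visit". It lists no enrollment measure of retention and no look-back period.

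**The concern.** Two things do not fit together.

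**Retention.** The model must carry the baseline value of an outcome counted in quarters of clinic attendance. Someone who is only now starting ART has no such quarters, and the protocol defines no baseline retention for anyone else either. An analyst following 6.7 literally has a missing covariate for an admitted group. Complete-case fitting removes those patients. Coding them as not retained puts them with people who did default.

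**Viral suppression.** A baseline value exists here, because viral load is measured at enrollment. It does not carry the information needed, though. An initiator and an established patient unsuppressed on ART have the same baseline value. The first can be expected to move toward suppression because treatment is starting, whatever the arm, and the second has no such reason to change. ART status therefore predicts the outcome within the baseline-unsuppressed group, and the models include it only if a significance test happens to flag it.

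At stake is the second specific objective, preliminary effectiveness on engagement in HIV care. Section 2.2 says the information gathered will lead to an application for a larger cluster-randomized trial.

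**Working it through.** The protocol gives no figure on this point to reproduce. The check has two parts.

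**1. Can the required covariate be formed?**

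| Outcome | Baseline source in 6.6 | Established patient | ART initiator |
|---|---|---|---|
| BDI-II | measured at enrollment | available | available |
| Viral suppression | viral load at enrollment | available | available, but does not show ART stage |
| Retention | none listed | could be abstracted, but no look-back is defined | no prior quarters to count |

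The rule covering all outcomes works for two of the three. For retention it is undefined for everyone and cannot be formed for initiators.

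**2. How far could ART status matter for suppression?**

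*Inputs from the protocol:* 35 per arm (6.5); 40-78% suppressed among those on ART (2.1).

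*Assumptions:* the share of initiators and their 12-month suppression rate. The protocol gives neither.

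*(a) Power of the balance test.* The calculation compares initiators with all others between two arms of 35, with shares s and s + 0.20, at two-sided 5%:

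power = Φ{ [0.20 − 1.96·√(2p̄(1−p̄)/35)] / √([s(1−s) + (s+0.20)(0.80−s)]/35) }, where p̄ = s + 0.10.

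For s = 0.30, the null SE is √(2·0.40·0.60/35) = 0.117 and the alternative SE is √((0.21+0.25)/35) = 0.115. Power is Φ{(0.20 − 0.230)/0.115} = 0.40.

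| Assumed initiator share s | SD of chance difference between arms, √(2s(1−s)/35) | Power to flag a 20-point imbalance |
|---|---|---|
| 5% | 5.2 points | 66% |
| 10% | 7.2 points | 55% |
| 20% | 9.6 points | 45% |
| 30% | 11.0 points | 40% |

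A simulated three-arm chi-square test, with one arm 20 points above the other two, gives about 75%, 63%, 48% and 42%. The conclusion does not change.

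*(b) Size of the distortion with no intervention effect.* If all 35 are treated as on ART, the protocol's range gives 35 × 0.22 = 7.7 to 35 × 0.60 = 21 unsuppressed per arm. Assume 45% of them are initiators, with 12-month suppression of 75% in initiators and 35% in the other unsuppressed patients, a 40-point gap. The SD of the between-arm difference in initiator share is √(2·0.45·0.55/n).

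| Unsuppressed per arm, n | SD of share difference | × 40-point gap (within stratum) | × n/35 (whole arm) |
|---|---|---|---|
| 8 | 24.9 points | 9.9 points | 2.3 points |
| 14 | 18.8 points | 7.5 points | 3.0 points |
| 21 | 15.4 points | 6.1 points | 3.7 points |

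The last column applies to the planned contrast, because 6.7 compares whole arms. A cruder range, before any adjustment for baseline viral load, multiplies a 10- to 30-point difference in initiator share by a 10- to 30-point difference in suppression. This gives 0.10 × 0.10 = 1 point to 0.30 × 0.30 = 9 points.

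*(c) Comparison with the noise.* The 95% half-width for a 35 v 35 difference is 1.96·√(2p(1−p)/35). This is 23.0 points at p = 0.40 and 19.4 points at p = 0.78.

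**The case against.** **The plan already adjusts for more than baseline values.** This stands. The models also take in clinic and any unbalanced confounder, so a gross excess of initiators in one arm could be caught. The weakness is the trigger: at this size the test misses a 20-point imbalance about as often as it finds one, and ART status is not named among the characteristics to be tested.

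**The contrast is still defined.** This also stands. A reader might infer that the engagement comparison is itself partly undefined. It is not: retention and suppression at follow-up exist for every participant, and only a covariate is missing.

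**Chance imbalance is not confounding.** Correct under individual randomization, where the confidence interval already reflects it. A reader might infer that ART stage confounds the arms. The protocol supports that only as a possibility, if clinics are the randomized unit, and it contradicts itself here. Section 1.0 and the opening of 6.1 describe an individual-level trial. Sections 2.0, 2.2 and 6.4 and the second sentence of 6.1 randomize clinics. With four clinics and three arms, a different initiator mix by clinic would be a structural difference that clinic adjustment could not separate from arm. Against that, 6.2 says the clinics were matched on patient population.

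**Dropping or miscoding is not the only choice.** True. A separate category for no attendance history would work, but that is initiator status under another name, and the protocol does not provide it.

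**This belongs in a statistical analysis plan, which may exist.** Look-back windows and coding often do. The difference is that the protocol itself fixes the rule, and its own eligibility clause makes that rule unworkable for an admitted group.

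**The stakes are low.** Largely true: the outcomes are secondary and preliminary, and the protocol states no hypotheses.

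**Conclusion.** The retention defect rests on the text alone. Section 6.7 requires a baseline value that 6.6 does not collect and that initiators cannot have.

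The suppression point is a weakness of method. A foreseeable prognostic factor is left to a baseline test with about 40-66% power (two-arm form, 20-point imbalance, assumed initiator shares of 5-30%).

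The numerical effect is modest. A reader might take the 6-10 points in the working as the distortion of the trial result. That figure holds only within the unsuppressed stratum, under an assumed 45% initiator share and 40-point outcome gap. Over a whole arm it is about 2-4 points, well inside a half-width of 19-23 points. Treating all 35 as on ART while also assuming initiators among them is a simplification, so these figures only show the order of size.

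The problem becomes structural only if clinics are the randomized unit, which the protocol must settle. Overall this is a cheap improvement to the analysis of secondary outcomes and does not invalidate the pilot.

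**What to change.** In 6.7, pre-specify ART status at enrollment (initiator, re-initiator, established) as a fixed covariate in the retention and viral suppression models, whatever the balance tests show. Pool initiators and re-initiators if cells are sparse. In the retention model, use this variable in place of the baseline value of the outcome. Keep baseline suppression in the viral suppression model.

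The text change is about two sentences, and ART status should be known when a patient is recruited at an ART clinic. The costs are one or two extra parameters per model, possible convergence problems in the log-link models at this sample size, and loss of earlier attendance history for established patients.

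Reporting suppression as maintained or gained within each of the three ART statuses is not worth adding. With roughly 8-21 unsuppressed patients per arm, the cells would be too small to read.

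The unit of randomization should be reconciled across 1.0, 2.0, 2.2, 6.1 and 6.4, because it decides whether an ART-stage imbalance is chance or structural.
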